### Economic evaluation

The economic evaluation is a combination of a cost effectiveness analysis (CEA) and cost utility analysis (CUA). In addition to the effect assessments the following instruments will be used: 1) a questionnaire on care use and participation, to gain insight in the costs for health care, the patient and his environment, and the costs outside the health care, 2) the EQ-5D-5L to gain insight into the generic quality of life and utilities. Both instruments are applied simultaneously with the outcomes measures of the effect study. To translate care use and participation in costs, the Dutch Manual for Costing in Economic Evaluations (*Nederlandse Handleiding voor Kostenonderzoek*) will be used [26]. The primary outcome measure for the CEA will be the MSSES control score at 6 months, and the primary outcome measure for the CUA will be the Quality Adjusted Life Years (QALYs). The QALY is a measure in which the number of life years is multiplied with a correction factor the quality of those life years, also called utility. The utilities will be calculated by means of the Dutch tariff that is actually being developed for the EQ-5D-5L. To enable a combined assessment of costs and effects the incremental cost effectiveness ratio (ICER) will be calculated, according to the following formula: $$ \mathrm{ICER}=\frac{\left({\mathrm{Costs}}_{\mathrm{intervention}}-{\mathrm{Costs}}_{\mathrm{control}}\right)}{\left({\mathrm{Effects}}_{\mathrm{intervention}}-{\mathrm{Effects}}_{\mathrm{control}}\right)} $$, wherein ‘Costs intervention’ represents the costs during the whole follow up period in the CDT group, ‘Costs control’ the costs during the whole follow up period in the control group (‘care as usual’), ‘Effects intervention’ the effects at the end of the follow up period in the CDT group, and ‘Effects control’ the effects at the end of the follow up period in the control group. To test for eventual uncertainties that may arise in an economic evaluation study, sensitivity analyses will be performed to assess whether different assumptions lead to different ICER outcomes. To gain insight into sample uncertainty bootstrap analysis will be performed. Based on the results of the bootstrap analysis the ICER uncertainty will be represented graphically. The probability that CDT is cost-effective will be represented with a cost effectiveness acceptance curve.

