**Methods/Design:**

CDT is a sociologically oriented approach, its goal is to uncover and promote existing capabilities, and the notion “stressor” is the central concept. CDT’s components are plenary group sessions, small group sessions, consultations, a theatre evening, and start of the day with a joint activity. The small group sessions form the actual training. Depending on their individual goals the participants join the training groups ‘Body’, ‘Feeling’ or ‘Life’, to work out their aims and to reduce their stressors. The multidisciplinary team includes a psychiatrist, psychiatric nurse, neurologist, specialized MS nurse, physiotherapist, dance therapist, and a person with MS. To evaluate the (cost)effectiveness of CDT in persons with relapsing remitting MS and low disability we perform a single-centre, randomized controlled trial in 140 patients, with or without support partners. The primary outcome is self-efficacy control. The secondary outcomes are self-efficacy function, health-related quality of life, autonomy and participation, anxiety, depression, cost effectiveness and cost utility. The tertiary outcome is care-related strain to support partners. Outcomes are assessed at baseline and at 1, 3 and 6 months after CDT.

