## Methods/Design

### Study design and organization

The study is a single-centre, parallel group, randomized, controlled trial to evaluate the clinical and cost effectiveness of CDT, with or without support partners, in increasing self-efficacy control in RRMS patients with low disability. The 3-day CDT is given to groups of 20 persons in Zorghotel Spelderholt, Beekbergen, The Netherlands, a facility especially equipped for the accommodation of people with impaired health. The first group was treated in April 2013. The ratio between the numbers of patients with support partner and without support partners is about 3:4. The CDTs are given from Friday to Sunday.

The control groups receive no CDT and may receive any care or treatments that are deemed necessary by the treating neurologists, MS nurses or other caregivers (‘care as usual’). In the experimental groups and the parallel control groups the baseline assessment is one week before the CDT, and in all groups the duration of follow-up is 6 months with assessments being performed at 1, 3 and 6 months.

The underlying idea of a 3-day social cognitive intervention program was conceived by the National MS Foundation The Netherlands, Rotterdam, The Netherlands (AvdZ), and further developed in collaboration with PsyToBe (RR, LD) and the other team members. The study is initiated, financed and conducted by the National MS Foundation The Netherlands, and the CDTs are organized and managed by this foundation (MvD). The contributions of the psychiatrist and the psychiatric nurse are part of regular care and are covered by the health insurance. The MS4 Research Institute is responsible for the scientific evaluations.

The study is ongoing (recruiting patients).

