### Statistical aspects

Based on the differences in MSSES control scores between baseline and at 6 months after CDT found in RRMS patients with EDSS score <4.0 in the explorative observational study [12], we conducted the following power analysis. We assume at 6 months an average of 650 for the experimental group and an average of 560 for the control group (an increase of 10 points compared to the baseline average found in the observational study). Assuming an SD of 200 on the 6 months measurement we would need 79 patients per group in order to obtain a power of 80 %, when using a two-sided t-test with an alpha of 5 %. However as we will use the baseline measurement in the analysis this number has to be multiplied by a design factor equalling 1 – r^2^_baseline, 6 months_. Assuming a correlation of 0.5 (also based on the observational data) this design factor equals 0.75. Therefore, the number of analyzable patients needed to obtain a power of 80 % equals approximately 60 per condition. Taking account of an expected drop-out of 15 %, we will include a total of 140 patients; approximately 60 with support partner and 80 without support partner.

The randomisation is performed by a statistician who is not otherwise associated with the study ([name] PhD, Signidat, Groningen, The Netherlands) via a stratified block randomisation with disease duration and gender as blocking factors. The randomisation list was made at the Department for Health Evidence (RD), Radboud university medical center, Nijmegen, The Netherlands.

The primary outcome variable is the MSSES control score after 6 months. This will be analysed using an ANCOVA with the assessment of 6 months as dependent variable and condition and baseline assessment as independent variables For all other variables the 6 months values will be analysed in a similar way. All analyses will be performed according to the intention-to-treat principle. The statistical analyses will be performed at the Department for Health Evidence, Radboud university medical center, Nijmegen, The Netherlands.

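### Incremental cost is defined on follow-up costs alone, with no stated use of the baseline care-use data; a baseline-cost covariate would be a cheap, minor gain in precision

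*Protocol article*

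**What the plan says.** All references are to the protocol article.

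- **Cost term.** Under Economic evaluation the ICER is printed as a difference in costs over a difference in effects. The intervention cost term "represents the costs during the whole follow up period in the CDT group"; the control term is "the costs during the whole follow up period in the control group". Neither contains a baseline cost.
- **Cost instrument.** Costs come from "a questionnaire on care use and participation, to gain insight in the costs for health care", among other cost categories. On timing, for this questionnaire and the EQ-5D-5L: "Both instruments are applied simultaneously with the outcomes measures of the effect study".
- **Visits.** The abstract states: "Outcomes are assessed at baseline and at 1, 3 and 6 months after CDT". Study design and organization adds that, in experimental and control groups alike, "the baseline assessment is one week before the CDT", and that "in all groups the duration of follow-up is 6 months with assessments being performed at 1, 3 and 6 months".
- **Effect analysis.** Under Statistical aspects, MSSES control at 6 months is analysed by ANCOVA with "condition and baseline assessment as independent variables". The 6-month values of all other variables are to be handled in a similar way.
- **Uncertainty.** Economic evaluation plans sensitivity analyses, a bootstrap and an acceptability curve. None of these mentions baseline costs.

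**The concern.** Taken together, the timing statements imply that care use is recorded in both arms one week before CDT, but the article gives that record no role in the analysis. The ANCOVA sentence does not clearly fill the gap: it speaks of 6-month values, whereas the cost term accumulates over the whole follow-up and has its own definition.

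A person's earlier and later care costs are usually correlated to some degree. If so, an unadjusted comparison leaves explainable variance in the interval for incremental cost. Any chance difference in prior care use that occurs in this trial also shifts the centre of the bootstrap cloud and the acceptability curve. Randomisation is stratified by disease duration and gender, not by prior care use, so the design does not itself limit that imbalance.

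The trial relies on the same principle elsewhere: it lowers its sample size because the primary outcome is adjusted for baseline. What is at stake is the efficiency of a secondary analysis, not its validity.

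**Working it through.** **1. The plan's own use of baseline adjustment (Statistical aspects).** Inputs: 6-month means 650 and 560 (difference 90), SD 200, two-sided alpha 5%, power 80%, baseline to 6-month correlation 0.5, drop-out 15%.

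- Two-sided t-test with standardised difference 90/200 = 0.45: n = 78.49, rounded up to 79 per group. This matches the stated figure.
- Design factor 1 − r² = 1 − 0.5² = 0.75; 79 × 0.75 = 59.25, rounded up to 60. This matches.
- 2 × 60/0.85 = 141.2, against 140 stated; close enough.

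So for self-efficacy the plan credits baseline adjustment with a 25% cut in variance.

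**2. The same formula applied to costs.** The article gives no cost SD, expected cost difference or baseline/follow-up cost correlation. Results are therefore in units of the cost SD, over an assumed range of r, with n = 60 analysed per arm.

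- Unadjusted SE of the cost difference: √(2/n) = √(2/60) = 0.183 SD.
- Adjusted SE: 0.183 × √(1 − r²).
- Unadjusted sample size with the same precision: 60/(1 − r²) per arm.
- Shift in the unadjusted cost difference from a baseline imbalance of one standard error: r × 0.183 SD.

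| Assumed r | Variance factor 1 − r² | Adjusted SE (SD) | Fall in SE | Equivalent n per arm | Shift from a 1-SE imbalance (SD) |
|---|---|---|---|---|---|
| 0 | 1.00 | 0.183 | 0% | 60 | 0 |
| 0.2 | 0.96 | 0.179 | 2% | 62.5 | 0.037 |
| 0.3 | 0.91 | 0.174 | 5% | 65.9 | 0.055 |
| 0.5 | 0.75 | 0.158 | 13% | 80 | 0.091 |
| 0.7 | 0.51 | 0.130 | 29% | 117.6 | 0.128 |

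The formula ignores the single degree of freedom spent on the covariate, which is negligible at this sample size.

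**3. How often an imbalance of some size arises.** The baseline cost difference also has SE 0.183 SD. For an imbalance of at least 0.2 SD in either direction, z = 0.2/0.183 = 1.10 and the two-sided probability is about 27%. This holds for any baseline variable with 60 per arm. It describes the setting and is not evidence of a flaw particular to this trial.

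**The case against.** The strongest reply is that the article prints the generic ICER definition. That says what is to be estimated and over which period, not how the group costs are estimated. A regression-adjusted cost difference, refitted in each bootstrap sample, satisfies the formula as written. The denominator supports this reading: it too has no baseline term, yet the cost-effectiveness outcome is MSSES control at 6 months, which is analysed with baseline adjustment. Covariates in a cost model are also the kind of detail that an article may leave to a fuller plan.

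This stands to a large extent. A reader might infer that the plan prescribes an unadjusted estimator; the text does not support that, since it neither states nor excludes adjustment.

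A reader might also infer that chance imbalance could decide whether CDT appears cost-saving or costly. The article gives no costs, cost SD, programme price or expected cost difference, so that cannot be shown.

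On harm, randomisation makes the unadjusted difference unbiased, and a bootstrap that resamples patients already reflects chance imbalance as sampling uncertainty. That stands too, with one limit: the bootstrap is centred on the observed estimate, so it widens the interval but does not correct the shift caused by the imbalance actually seen.

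Finally, r may be low. Entry requires no relapse in the preceding 4 weeks, while patients who relapse during follow-up stay in the study. If the baseline recall window is short, baseline costs would miss relapse care that follow-up costs include. The article does not state the window, so a small gain is a real possibility.

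What remains is that the economic section defines its cost terms in words and names its uncertainty methods, and followed literally it leaves baseline care-use data unused. It also leaves open whether an adjusted or an unadjusted cost difference is reported.

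**Conclusion.** The point holds as a minor one. The cost difference as literally defined is unbiased and its bootstrap interval valid, but it may be less precise than the available data allow, and it carries any observed chance imbalance in prior care use. With 60 analysed per arm, adjustment would lower the SE of incremental cost by 0% to 29% for r between 0 and 0.7, and by 13% at 0.5, the value the plan assumes for self-efficacy. No value of r for costs can be taken from the article.

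The conclusion rests on two readings: that the care-use questionnaire is completed at baseline, which follows from the timing statements but is not said outright, and that the ANCOVA sentence for 6-month values does not reach cumulative costs. It concerns the cost numerator only.

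**What to change.** Add one sentence to Economic evaluation. Incremental cost is the condition coefficient from a linear regression of follow-up cost on condition and baseline cost, with baseline care use valued by the same costing manual. The model is refitted in each bootstrap sample together with the baseline-adjusted effect model, and the ICER and acceptability curve are built from those paired estimates. Keep the unadjusted difference as one of the planned sensitivity analyses. If a fuller plan already says this, a cross-reference is enough.

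The cost is that sentence and a few lines of code; no new data are needed. The downside is small. Because the baseline recall window is not stated and may be shorter than the 6-month follow-up, baseline cost should enter as a covariate and not be subtracted as an offset, and the gain may turn out small. Stating the recall window and confirming the baseline administration would settle both uncertainties.

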## Discussion

In an exploratory observational study we assessed in people with MS the potential effectiveness and feasibility of an intensive social-cognitive program with the participation of support partners and found that in the RRMS subgroup self-efficacy control, mental HRQoL and physical HRQoL had increased by 24.8 %, 22.3 % and 17.6 %, respectively. Likewise, in persons with low disability (EDSS score 4.0 or less) the self-efficacy control and mental HRQoL had increased with 23.8 % and 19.3 %, respectively. No such changes were seen in the progressive subgroup or in persons with higher disability (EDSS > 4.0). Therefore, we conceived a randomized controlled trial to further evaluate the (cost)effectiveness of CDT in people with RRMS and low disability. Several other observational studies showed beneficial effects of various types of social-cognitive wellness programs in MS [11, 27, 28], but as yet there are no reports of randomized controlled trials [29].

We considered the MSSES control score the main outcome measure, and not the MSSES function or total score, because the pilot study showed an evident difference between the change in the self-efficacy control vs. the absence of change in self-efficacy function (+1.2 %) [12]. Conceptually, the control and functional subscales of the MSSES measure different dimensions of self-efficacy: the control subscale measures confidence with managing symptoms and coping with the demands of illness, whereas the function subscale measures confidence with functional abilities.

Having had a relapse in the preceding 4 weeks is an exclusion criterion, since we considered that being in a suboptimal condition due to clinical disease activity would increase the risk of unwanted side effects, and would also interfere with the efficacy of CDT. Participants with a relapse during the study period are not excluded from the study, as we do not expect that having experienced a relapse in the 6 month study period or experiencing a relapse at the month 6 assessment does substantially affect self-efficacy; self-efficacy is considered a rather stable trait that requires an intense intervention like CDT to be modified. To address this point in the analysis phase, we assess the on-study occurrence of relapses and will perform a stratified secondary analysis to assess an eventual effect of relapses on the primary outcome.

In an extension phase of 6 months duration we will assess the effect of CDT in the longer term. After the patients in the intervention arm of the study have completed the study they are eligible to be followed for another 6 months, and patients in the control arm have the option to receive the CDT and are also eligible to be followed for another 6 months. Thus, we will be able to assess whether the effect of CDT is sustained on the longer term (12 months), and to assess whether in the control group a similar change in self-efficacy control occurs after CDT as in the RCT intervention group.

An important aspect of complex interventions is their feasibility in real life, e.g. in terms of drop outs, logistics and costs. The drop-out percentage during the 3-day intervention in the pilot study was low (7.4 %) [12], which suggests that the drop out in real life conditions may be limited. As to logistics, in the RCT all CDTs are given at one central location in The Netherlands, as was the case in the pilot study. After the RCT the CDTs will also be given at this location, which has been proven to be easy accessible and well-equipped. Similar approaches could be taken in other countries. A practical aspect of CDT’s implementation and embedding in MS care are the costs in relation to the clinical effects; to be able to weigh the benefits against the costs we investigate the cost-effectiveness of CDT.

Finally, it may be conceived that CDT is influenced by specific aspects of the Dutch health care system and could therefore be of less interest to people with MS treated in other countries. It is of note that a comparable treatment, the Can Do Program, is being given to people with MS in the U.S.A. and improvement in self-efficacy and perceived health was observed in patients who took part in this program [11]. Moreover, none of the components of CDT is related to specific aspects of the Dutch health care system or the Dutch culture. Therefore, in terms of content and effectiveness no relevant differences between countries are to be expected. Yet, the implementation of the study results will depend on the incorporation of CDT in the regular care process, which may differ between countries given the differences in health care systems and reimbursement policies.

## Abbreviations

CEA: cost effectiveness analysis
CDT: can do treatment
CSI: caregiver strain index
CUA: cost utility analysis
EDSS: expanded disability status scale
EQ-5D-5L: euro quality of life 5 dimensions 5 levels
HADS: hospital anxiety and depression scale
HRQoL: health-related quality of life
ICER: incremental cost effectiveness ratio
IPA: impact on participation and autonomy
METC: medische ethische toetsing commissie
MS: multiple sclerosis
MSSES: multiple sclerosis self-efficacy scale
MSQoL-54: multiple sclerosis quality of life-54 items
RRMS: relapsing remitting multiple sclerosis
QALY: quality adjusted life year
SPMS: secondary progressive multiple sclerosis
UCL: Utrecht coping list
